TRE is a promising field of study and has gained traction in the media and the public over the past decade for its ability to strengthen circadian rhythms and improve health [19–21]. TRE involves restricting the consumption of calories to a short window (4–12 h) during normal waking hours, for example 8am-6pm; water is never restricted. Human (time-restricted *eating*) and rodent (time-restricted *feeding*) studies have shown that TRE helps to maintain metabolic homeostasis and, as a result, helps with weight management, improves sleep, and attenuates age- and diet-induced heart disease (review [20]). Hatori et al. clearly demonstrated the effects of nutrient timing on metabolic regulation: time-restricted feeding vs. time-*un*restricted feeding of mice led to weight loss despite equal energy intake [22]. In humans, Gabel et al. performed a single-arm 8-h TRE study among obese adults for 12 weeks (*n* = 23) [23]. Despite the diet being *ad libitum*, caloric intake decreased 341 ± 53 kcal/day; body weight decreased 2.6 ± 0.5%, and systolic blood pressure decreased 7 ± 2 mmHg. However, there were no significant changes in body composition, circulated lipids, fasting blood glucose, or fasting insulin. Also, Wilkinson et al. performed a single-arm 10-h TRE study among patients with metabolic syndrome for 12 weeks (*n* = 19) [11]. They observed improvements in sleep efficiency and quality, a safe rate of decrease in body weight and body fat percentage, a reduction in total and low density lipoprotein (LDL) cholesterol, and reductions in systolic and diastolic blood pressure [11]. While these studies were implemented for 12 weeks, benefits of an 8-hour TRE window have been seen in glucose and lipid metabolism and circadian clock gene expression in as short as 4 days [24].

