### Eligibility criteria

Inclusion criteria (*Participants must*…):

Have a diagnosis of a hematologic neoplasm (e.g., leukemia, lymphoma, multiple myeloma);Be at least 2 months post-treatment with chemotherapy, radiation, targeted therapy, chimeric antigen receptor (CAR)-T cell therapy, stem cell transplant, or another therapy (maintenance therapies are acceptable; steady unchanged treatment for relapsed disease for > 2 months and expected to stay on the therapy until progression is also acceptable);Have a baseline level of fatigue, as determined by at least one of the following:
Reporting a score of 4 or higher in response to the question, “What was your worst fatigue in the last week, on a scale of 0–10, where 0 is no fatigue and 10 is the worst fatigue?”In the habit of taking daytime naps,Have fatigue that interferes with their ability to work, engage in social events, or is more than would be expected from physical exertion,
Be able to speak and/or read and write in English or Spanish;Be at least 18 years old; andBe able to provide informed consent.

Exclusion criteria (participants must not…)

Be underweight, as defined as a body mass index < 18.5 kg/m^2^;Already eat all their food within a window that is 10 h or shorter most (6/7) days of the week (for this criterion, we ask when they typically have their first beverage or bite of breakfast in the morning, and when they typically have their last meal, snack, or beverage before bed; if this window is > 10 h the person is eligible; people who often eat during sleeping hours are also eligible);Be employed in a job where they regularly work away from the home at night (e.g., night shift);Have surgery planned during the study duration;Have any contraindications to the proposed nutrition intervention as identified by their medical provider, their designee, or the study team (e.g., type 1 diabetes, risk for hypoglycemia, medication requirements, pregnancy or plans for pregnancy, breastfeeding, recent history of an eating disorder);Be taking insulin; orBe on enteral or parenteral nutrition.

While taking part in this study, participants may concomitantly be part of drug trials or observational trials but may not be part of other trials that are testing behavioral interventions.

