### Time-restricted eating (TRE) intervention

Those randomized to TRE self-select a 10-hour eating window based on their schedule and preferences. We encourage the eating window to be during the daytime hours and end approximately 3 h before bedtime. This window should be consistent for the 12-week study duration. Aside from water, which is always allowed, only unsweetened tea and black coffee are allowed before the eating window. Calorie-free foods and beverages such as chewing gum, diet soda, and herbal tea, are discouraged outside the eating window. Participants in the TRE group meet with the same dietitian as those in the control group for individualized nutrition counseling, and goals discussed during the counseling session are asked to be met within the eating window. To match expectancy [46], the two interventions are presented as having a potentially equal benefit on their fatigue (“We are testing two nutritional interventions, both of which should help with your fatigue, one of them has a time component and the other does not”). Those in the TRE group will meet with the same dietitian 7 times throughout the 12-week study, matching the frequency of those in the control group.

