### Outcomes

#### Adherence

Eating windows are assessed using the myCircadianClock smartphone application [41] or paper-based logs if requested. This app uses a camera to capture meals and saves entered food items to facilitate data entry. The app has additional features to log sleep, exercise, and medications at the participants’ discretion. This app is user-friendly and has been used in several circadian rhythm clinical trials [11, 17] including cancer populations (e.g., NCT05083416, NCT04783467 [34]). The length of the eating window will be extracted for each participant for each day. Some of our participants have medication requirements that are outside the eating window and recommend concurrent food consumption; if only a small amount of food is ingested (< ~ 25 kcal), this is not included in the eating window. The following parameters will be calculated: (1) how many days the participants ate within a 10-h window, and (2) the average length of the eating window. A participant will be considered “adherent” if they ate within the 10-h window at least 6/7 days (at least 80% of days, measured weekly). (While some TRE protocols build in one or two “cheat” days [33, 47], this is not included as part of our teaching. Also, other protocols use a “95% eating window,” in which 95% of all calorie-containing ingestion events occur [11]. However, we are not confident that we will obtain accurate calorie information at each eating instance to calculate a 95% eating window.) Adherence information will be used in secondary analyses of the effects of TRE on fatigue and other outcomes.

It is likely that there will be some non-adherence in the TRE group, and possible that contamination will exist in the control group, i.e., controls following TRE. Therefore, a secondary per-protocol analysis will be performed in addition to an intent-to-treat analysis.

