#### Data analysis

Prior to hypothesis testing, the demographics and patients’ characteristics will be compared between TRE vs. control groups and the relevant variables (e.g., age) that differ by group will be included as confounders in hypotheses testing. To provide estimates of efficacy comparing TRE vs. an unrestricted eating pattern to alleviate fatigue, the first objective is to longitudinally evaluate the between-arm difference in mean change in MFSI score from baseline to post-intervention (12 weeks after baseline) in a linear mixed model. A data collection point at 6 weeks is also included in order to capture any effects of the intervention at a shorter time point. The outcome will be MFSI score and the fixed effects will include arm (TRE vs. control), time (baseline, 6, and 12 weeks), and interactions between arm and time. Statistical significance of the arm×time interaction will be assessed at an alpha of 0.05. Participants will be included as a random effect accommodating the correlations between repeated measures. If any aforementioned potential confounders (e.g., age, body mass index, psychological symptoms, time since completion of treatment) are not evenly distributed between the two groups, they will be added to the model. The results of the analyses together with the estimates of distribution parameters (e.g., mean, SD) of MFSI values as well as the change scores will be used in planning future randomized trials. In addition to statistical significance, we will assess the effect sizes and whether any changes seen are clinically meaningful. The MFSI has a published MCID of 4.5 points [49].

A second objective is to assess the sustainability of TRE three months after the intervention. At 24 weeks, follow-up will occur with several questionnaires. Participants will be asked to self-report the time of their typical first food/beverage intake and their typical last food/beverage intake at night over the previous week. The eating window will be calculated, and its length will be compared between arms using a t-test. We will also evaluate the proportion of patients adhering to 10-h window. We hypothesize those in the intervention group will have adopted a significantly shorter eating window than those in the control group.

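### The week-24 eating window counts any beverage, although TRE permits water, black coffee and unsweetened tea outside the window, so a participant who keeps to TRE can be scored as outside 10 h

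*Protocol article*

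**What the plan says.** All references are to the Protocol article.

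- **Background** defines the exposure by energy intake: "TRE involves restricting the consumption of calories to a short window (4–12 h) during normal waking hours". It adds that water is not restricted.
- **Time-restricted eating (TRE) intervention** gives the rule taught to the TRE arm: "Aside from water, which is always allowed, only unsweetened tea and black coffee are allowed before the eating window". Other calorie-free items, such as diet soda and herbal tea, are discouraged outside the window.
- **Adherence** covers the on-study measure from the app or paper log. For food taken with medication outside the window it says "if only a small amount of food is ingested (< ~ 25 kcal), this is not included in the eating window".
- **Data analysis**, second objective, says that at 24 weeks participants "self-report the time of their typical first food/beverage intake and their typical last food/beverage intake at night", with reference to the previous week. It continues: "The eating window will be calculated, and its length will be compared between arms using a t-test". It then adds: "We will also evaluate the proportion of patients adhering to 10-h window". The stated hypothesis is a shorter window in the TRE arm.
- **Procedures** says that week 24 consists of questionnaires alone, so no food log is described that could correct the two reported times.

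**The concern.** The intervention and its week-24 measure use different definitions of the eating window. TRE participants are taught for 12 weeks that certain drinks do not break the fast. At week 24 the same drinks, if reported, set the start or end of the window. A participant who has kept exactly to what was taught can therefore be recorded as having given it up.

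The second objective is at stake. The proportion within 10 h is the direct measure of whether TRE was maintained, and the t-test on window length is the only between-arm test named for it. The article intends the data to inform a phase III trial, so an understated maintenance rate would carry forward into that planning.

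**Working it through.** The documents give no expected week-24 window, SD, adherence rate or frequency of early drinks, so there is no figure of theirs to reproduce. The contradiction follows from the text alone. Its size can only be illustrated.

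**Step 1: the two definitions applied to one person.** Black coffee at 06:30, first food at 09:00, last food at 18:30.

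- Window as taught (food only): 18:30 − 09:00 = 9.5 h, within 10 h.
- Window by the week-24 question, answered literally: 18:30 − 06:30 = 12 h, outside 10 h.

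**Step 2: who is affected.** Let W be the true food window and h the time from a permitted drink to first food. A person is misclassified only if W ≤ 10 < W + h and the drink is reported. Someone with W ≤ 10 − h stays within 10 h either way. Coffee and tea are permitted only before the window, so at the end of the day only water is clearly permitted.

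**Step 3: illustration for the 10-h proportion (all inputs assumed).** Take W in the TRE arm as Normal with mean 9.5 h and SD 1 h. A share q has, and reports, a permitted drink h hours before first food.

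- True proportion within 10 h: Φ((10 − 9.5)/1) = Φ(0.5) = 69%.
- With q = 50% and h = 1 h, the measured proportion is 0.5 × Φ(0.5) + 0.5 × Φ(−0.5) = 0.5 × 0.69 + 0.5 × 0.31 = 50%. By simulation, 28% of the truly adherent are misclassified.
- With q = 25% and h = 0.5 h, the measured proportion is 64% and 7% of the truly adherent are misclassified.
- With q = 100% and h = 2 h, the measured proportion is 7% and 90% are misclassified.

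True means of 9 h or 10 h change the figures but not the direction.

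**Step 4: illustration for the t-test (all inputs assumed except n).** The mean window in an arm lengthens by q × h; for example, 0.5 × 1 h = 0.5 h. Only the lengthening in TRE net of control matters. The table uses 38 per arm (the article's evaluable number), a true difference of 2 h and a two-sided 5% test, with the SD held fixed.

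| Net lengthening in TRE | Measured difference | Power, SD 2 h | Power, SD 2.5 h | Power, SD 3 h |
|---|---|---|---|---|
| 0 h | 2.0 h | 99% | 94% | 83% |
| 0.5 h | 1.5 h | 91% | 74% | 59% |
| 1.0 h | 1.0 h | 59% | 41% | 31% |

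If control windows lengthen by the same amount, the first row applies and the mean difference is intact. The 10-h proportion in the TRE arm is still understated.

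**The case against.** **The article is not the questionnaire.** The form is not shown and may tell respondents to ignore water or black coffee. That is possible, and the text would then only need correcting. But the article does state the content of the question, it names beverages explicitly, and it states no exclusion. This is a stated rule that conflicts with another stated rule, not a detail left to a fuller document. A later analysis plan could not recover a first-calorie time that was never asked.

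**Not every adherent participant is affected.** This stands. A reader might infer that adherent TRE participants will in general be scored as non-adherent. Step 2 shows that only those who use the allowance, report it and then exceed 10 h are.

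**The direction of any between-arm bias is not documented.** This also stands. A reader might infer that the error falls mainly on TRE and pulls the comparison towards no difference. That is plausible, because delaying first food can widen the gap after an early coffee. But controls may also have early coffee or bedtime water. They are also not told to avoid diet soda or herbal tea late in the day, so their windows could lengthen as much or more.

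**Non-comparability with weeks 0 to 12 is not shown.** A reader might infer it from the Adherence section. The only exclusion stated there concerns small amounts of food taken with medication. It does not say how logged coffee or water is handled, and the planned week-24 test is between arms rather than against earlier weeks.

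**Screening is a separate matter.** A reader might extend the point to the Eligibility criteria, where "we ask when they typically have their first beverage or bite of breakfast in the morning". That item is worded differently, under a criterion about food. Any over-inclusion precedes randomization and cannot bias one arm against the other. The time-stamped baseline log can also show who already ate within 10 h.

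**Conclusion.** The point holds for week 24. As written, the measure can score a participant who follows the TRE rules as outside the 10-h window, so the proportion within 10 h can be understated. Dilution of the difference in window length is possible but conditional on a wider drink-to-food gap in TRE than in control.

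Neither effect can be sized from the documents. The percentages above show sensitivity to assumed inputs and are not estimates for this trial. The conclusion assumes that participants answer the question as the article describes it. It concerns a secondary objective and leaves the primary MFSI analysis untouched. It is worth correcting because the correction is cheap and the information cannot be recovered afterwards.

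**What to change.** Use one definition of the eating window in the TRE intervention, Adherence and Data analysis sections. At week 24, ask for the typical first and last food or calorie-containing drink. State on the form that the drinks permitted by the intervention section, and the small medication-related intake excluded in the Adherence section, do not count. Compute both the t-test and the 10-h proportion from these times.

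The definition should also say how the discouraged calorie-free items, such as diet soda and herbal tea, are scored. A calorie-based question leaves them out, although the intervention section advises against them outside the window.

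The cost is rewording in English and Spanish, an IRB amendment, and two question wordings within one outcome. Recruitment opened in September 2024 and is expected to run through 2027, so many week-24 assessments probably remain. Participants who answered the present wording should be flagged and separated in a sensitivity analysis. The screening item need not change during recruitment, since the logged baseline window can describe anyone who already ate within 10 h.

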**Methods:**

This trial is a phase II randomized controlled trial comparing the effects of time-restricted eating (10 h daytime feeding/14 h fasting at night) vs. a time-, attention, and expectancy-matched control nutrition counseling intervention (no time component) on cancer-related fatigue. A total of 96 blood cancer survivors will be recruited; eligible survivors will be 2 months to 2 years post-adjuvant chemotherapy, report moderate to severe fatigue, consume food within a window that is > 10 h, and not be employed in night-shift work. At baseline, 6 weeks, and 12 weeks (post-intervention), assessments include patient-reported fatigue, measures of circadian rest-activity rhythm, and glucose metabolism via continuous glucose monitoring. Participants will log their food intake using the myCircadianClock smartphone app at baseline and throughout the 12-week study. At 24 weeks (12 weeks post-intervention), questionnaires will probe maintenance of the dietary pattern and sustainability of any intervention effects on fatigue.

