## Methods

### Study overview

#### Study design

This is a phase II, parallel-group, RCT testing the effects of TRE vs. a nutrition control on cancer-related fatigue. Funded by the National Cancer Institute (NCI; R01CA284082), the trial is being conducted through the University of Maryland Medical System (NCT06482515, registered June 25, 2024). The primary aims are to provide initial estimates of efficacy of a 12-week TRE intervention vs. an unrestricted eating pattern on patient-reported fatigue among survivors of hematological malignancies experiencing fatigue. A secondary aim is to examine the sustainability of TRE and its effects on fatigue at 24 weeks. Mechanistic aims will assess the effects of TRE vs. control on circadian rest-activity rhythms and glucose metabolism, as well as assess associations between these measures. The study’s name is “Take the Reins,” which reflects how changing one’s diet can empower someone to control at least one aspect of their life that may have direct effects on their symptoms and healing.

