#### Fatigue

Patient-reported fatigue is the primary outcome, as measured using the Multidimensional Fatigue Symptom Inventory-Short Form (MFSI) [39] which captures five dimensions—general, physical, emotional, and mental fatigue, and vigor. The 30-item fatigue subscale has been validated among patients with cancer [48] and has a published minimal clinically important difference (MCID) of 4.5 points [49]. As an exploratory measure, the BFI [50] is also being administered, which captures fatigue in the last 24 h and how fatigue has interfered with activities. Questionnaires will be administered at baseline, week 6, week 12, and week 24.

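### The 24-week analysis leaves the collected baseline eating window unused and names no model for week-24 fatigue, which is part of the stated aim

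*Protocol article*

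**What the plan says.** **The aim.** The Study design section gives the 24-week aim two parts: "A secondary aim is to examine the sustainability of TRE and its effects on fatigue at 24 weeks". The abstract's Methods paragraph agrees, saying that at 24 weeks "questionnaires will probe maintenance of the dietary pattern and sustainability of any intervention effects on fatigue".

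**The data.** The Fatigue section, which covers the MFSI, says "Questionnaires will be administered at baseline, week 6, week 12, and week 24". Baseline eating times come from two sources. The eligibility question asks about usual first and last intake (Eligibility criteria), and food is logged with time stamps during the baseline week (Procedures).

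**The analysis.** The Data analysis section restates the objective with one part: "A second objective is to assess the sustainability of TRE three months after the intervention". Self-reported first and last intake at week 24 give a window, and "The eating window will be calculated, and its length will be compared between arms using a t-test". It adds: "We will also evaluate the proportion of patients adhering to 10-h window". The only hypothesis given for this objective concerns window length. The one MFSI model stated has fixed effects for arm, "time (baseline, 6, and 12 weeks), and interactions between arm and time". On covariates, the section says that "the relevant variables (e.g., age) that differ by group will be included as confounders in hypotheses testing".

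**The concern.** There are two separate problems, of unequal weight.

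**Fatigue.** Fatigue is the trial's primary measure and its persistence after the intervention is part of a declared aim, but no stated analysis uses the week-24 MFSI. If this stays open, the week-24 fatigue result could be produced by a method chosen after the data are seen. The article says its data will inform a phase III trial, and durability of effect is one of the things such a trial would want to know.

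**Eating window.** The named test compares week-24 windows alone. A baseline measurement of the same quantity is available and usually carries some information about the later value. Leaving it out gives up precision and leaves the estimate open to whatever chance imbalance in baseline window arises.

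**Working it through.** **1. Aim against analysis (fatigue).** No arithmetic applies, so the sections are set side by side.

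| Place | Maintenance of eating pattern | Fatigue at week 24 |
|---|---|---|
| Abstract, Methods | yes | yes |
| Study design | yes | yes |
| Fatigue (data collection) | – | MFSI collected |
| Data analysis, second objective | t-test and 10-hour proportion | not mentioned |
| Data analysis, MFSI model | – | time stops at week 12 |
| Data analysis, mechanistic objectives | – | similar models for rest-activity and glucose only |

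Stopping at week 12 is right for the primary model, because the primary endpoint is change from baseline to 12 weeks. The gap is that no second model is named for a stated aim.

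**2. The plan's own sample-size figure.** No sample size or power is given for the 24-week objective. The Sample size section gives n = 76 (38 per arm), 80% power, 0.50 SD, correlation 0.60 between MFSI scores and two-sided 0.05, all for the primary endpoint. It reproduces if the contrast is the mean of weeks 6 and 12 minus baseline:

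- variance = 1 + (1 + 0.60)/2 − 2 × 0.60 = 0.60, so SD = 0.775
- power = Φ(0.50 / (0.775 × √(2/38)) − 1.96) = Φ(2.81 − 1.96) = 80.3%

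This confirms the formula and supplies 38 per arm. It says nothing about week 24.

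**3. Eating window, unadjusted.** In units of the week-24 window SD:

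- standard error = √(2/38) = 0.229
- power for 0.50 SD = Φ(0.50/0.229 − 1.96) = Φ(2.18 − 1.96) = 58.7%
- difference detectable with 80% power = (1.960 + 0.842) × 0.229 = 0.643 SD

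**4. Eating window, adjusted for baseline.** The residual SD becomes √(1 − r²), where r is the correlation of baseline with week-24 window. The documents do not give r, so it is an assumption shown over a range.

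| Assumed r | Variance removed (r²) | Detectable difference (SD) | Power for 0.50 SD |
|---|---|---|---|
| 0 (t-test) | 0% | 0.643 | 58.7% |
| 0.2 | 4% | 0.630 | 60.4% |
| 0.3 | 9% | 0.613 | 62.7% |
| 0.4 | 16% | 0.589 | 66.2% |
| 0.5 | 25% | 0.557 | 71.1% |
| 0.6 | 36% | 0.514 | 77.8% |

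The 0.50 SD is only a yardstick borrowed from the fatigue calculation. The article states no expected difference or SD for the window.

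**5. Where r is likely to lie.** Three features point to the low end. Eligibility largely removes baseline windows of 10 hours or less, which restricts range. The intervention is meant to change the window in one arm. And the week-24 value is a recalled typical day, whereas the baseline log is a prospective record. The eligibility question is closer in form to the week-24 item than the log is.

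**The case against.** **The t-test is legitimate.** A two-sample comparison of randomised arms is unbiased, and choosing it for a secondary behavioural outcome is not an error. This stands in full: the eating-window half is a gain in precision, not a correction of a wrong method.

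**Imbalance and missing data are covered elsewhere.** This stands in part. The covariate rule acts only on variables found to differ between arms and does not name eating window, and a t-test takes no covariate. Baseline adjustment also gains precision when the arms happen to be balanced. On missing data, a reader might infer that the week-24 comparison simply drops non-responders. The article does not support that. Data organization and cleaning provides multiple imputation or maximum likelihood once more than 5% is missing, and sensitivity models if data are suspected to be missing not at random. Complete-case results are reported only if the estimates are similar. A baseline-adjusted linear model would itself lose non-responders without those rules.

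**The fatigue model may be in a fuller document.** An article condenses, and no sentence says week-24 MFSI will go unanalysed. A reader might infer that sustained fatigue will never be tested; that goes further than the text. What stands is narrower: the article does spell out an analysis for this objective and does list the model's time points, and neither matches the aim it states twice.

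**The objective is not answered by the t-test alone.** Correct: the proportion within 10 hours is evaluated too. That is still eating window, and no method is named for it.

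**Conclusion.** The point holds in two parts. First, the stated 24-week aim and the stated analysis do not match: sustained fatigue is in the aim and the data are collected, but no model is named. This is the weightier part and rests only on the text. Second, the eating-window comparison leaves a collected baseline value unused. The likely gain is small, about 2 to 4 percentage points of power at r of 0.2–0.3, and reaches about 19 points only at r = 0.6. These figures assume 38 per arm still evaluable at week 24, a normal approximation and an assumed r.

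Two stronger readings are not supported. The 0.60 in the Sample size section is for repeated MFSI scores and cannot be carried over to eating window, so the upper figure is not an expected gain. Nor can a firm power be attached to week-24 fatigue. With 38 per arm and r = 0.60, a change-from-baseline contrast would have about 68% power for 0.50 SD, and a baseline-covariate analysis about 78%. However, the article does not say that this sample, this correlation or an effect of that size applies 12 weeks after the intervention ends.

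The primary 12-week analysis is unaffected. This should be settled before analysis, but it does not threaten the trial.

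**What to change.** 1. **Eating window.** Replace the t-test with a linear model of week-24 window on arm and baseline window, reporting the adjusted difference with a 95% CI. Preferably take the baseline value from the eligibility question, which matches the week-24 item, with the baseline-week log as fallback. Use the same covariate for the 10-hour proportion, for example in a logistic model. State that the existing missing-data rules apply to both.
2. **Fatigue.** Restore fatigue to the second objective in Data analysis. Keep the 12-week primary model as it is: adding a visit to it would turn the arm-by-time test from 2 to 3 degrees of freedom and change the primary question. Add a secondary MFSI mixed model with time at baseline, 6, 12 and 24 weeks, and name the arm contrast in change from baseline to week 24, with a 95% CI, as the sustainability estimate.

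The cost is analysis-plan wording. No new data are needed, provided the answers to the eligibility question were kept; the article does not say whether they are stored. Recruitment is expected to run through 2027 with primary results in 2028, so both changes can be made before the data are analysed.
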